### Randomisation

A computerized random number generator draws up an allocation schedule pre-stratified for the hospital where participants will be measured or where they will follow the exercise program; within hospitals respondents will be allocated at random to either the intervention or to the control group. Block randomisation in blocks of four will be performed. After baseline measurements, a research assistant will inform the women about the group they will be allocated to.

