### Recruitment

Women will be recruited at the Departments of Obstetrics of VU University Medical Centre (VUMC), St. Lucas Andreas Hospital (SLAZ) and Onze Lieve Vrouwe Gasthuis (OLVG) in Amsterdam and 10 midwifery practices in Amsterdam. The obstetricians or midwives in the 3 hospitals and midwifery practices will introduce the study at the first visit of every pregnant woman who is eligible for inclusion. They will give the pregnant women who are interested to participate a brochure about the study to read at home. Obstetricians and midwives will also fill out a reply coupon (name, telephone number, inclusion and exclusion criteria) and will send this coupon to the research team. Interested women can return the informed consent form to the research team or the research team calls within two weeks after receiving the reply coupon. When women meet the inclusion criteria and want to participate, they will be included. After inclusion, an appointment for the baseline measurement will be made.

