### Sample size

Power analysis is based on the effects of the intervention program on fasting plasma glucose. A difference of 0.4 mmol/l in fasting plasma glucose between the two research groups is considered to be clinically relevant. Assuming a standard deviation of 0.7 mmol/l, this difference can be detected with a power (1-β) of 0.80 and an alpha of 0.05 with two groups of 64 subjects. Taking a loss to follow up of about 20% into account, a total of 160 subjects will be recruited. A significant difference of 300 grams in birth weight can also be detected with this number of participants, assuming a standard deviation of 600 grams.

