### Blinding

The key of coding concerning group assignment will only be known to the programmer of the database. The researcher and research assistant will not be blinded for allocation after randomisation. All outcome measures will be assessed by independent examiners, unaware of group allocation. Participants cannot be blinded for the intervention, but will be asked not to reveal information about their treatment to the examiners. Also obstetricians and midwifes cannot be blinded for the allocated treatment. Analyses will be performed blind for treatment allocation.

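### A single fixed block size of four within hospital, with unblinded research staff on a team that handles consent and contact, leaves up to one allocation in three deducible just before it is made

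*Protocol article*

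**What the plan says.** All references are to the Methods of the protocol article.

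- **Randomisation:** "A computerized random number generator draws up an allocation schedule pre-stratified for the hospital where participants will be measured" or will exercise, and "Block randomisation in blocks of four will be performed". No variation in block size is stated, and nothing says that the size is withheld from the research staff. The same section adds: "After baseline measurements, a research assistant will inform the women about the group they will be allocated to".
- **Blinding:** the key to the group codes is held by the database programmer alone, but "The researcher and research assistant will not be blinded for allocation after randomisation". Outcome examiners are to be unaware of allocation, and the analysis is to be done blind.
- **Recruitment:** the obstetrician or midwife completes a coupon covering the entry criteria and sends it to the research team. The woman returns her consent form to that team, or "the research team calls within two weeks after receiving the reply coupon". Then: "When women meet the inclusion criteria and want to participate, they will be included". The baseline appointment follows. No one is named as the person who decides on inclusion.
- **Sample size:** the calculation works "with two groups of 64 subjects", and with allowance for dropout "a total of 160 subjects will be recruited".

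**The concern.** In blocks of one known size, the last places follow from the earlier ones. Holding the list with the programmer keeps the list itself secret, but it does not prevent deduction from allocations that have already been announced. The staff who know those allocations belong to the team that receives consents and telephones the women.

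Someone who foresees the next arm can, without intending to, influence whether a woman enters or when her baseline visit takes place. There is room for this: one entry criterion, the ability to be moderately active, is a judgement, and the entry window runs from 14 to 20 weeks. If women expected to attend exercise sessions were steered towards the intervention arm, the groups would differ in motivation from the start. Blinded examiners guard against biased measurement, and blinded analysis against biased analytic choices. Neither acts on who enters which arm.

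**Working it through.** The article gives no figure for predictability, so there is none to reproduce.

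**Inputs.** Block size 4 (Randomisation); three hospitals as strata (Recruitment, Intervention Group); 160 women (Sample size). A 1:1 ratio is inferred from the equal groups, so each block holds two of each arm.

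**Share certain just before allocation.** There are six equally likely blocks: AABB, ABAB, ABBA, BAAB, BABA, BBAA. An allocation is certain once one arm of its block is full.

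- 1st and 2nd places: never.
- 3rd place: when the first two match, in 2 of 6 blocks, probability 1/3.
- 4th place: always.

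Certain allocations per block = 1/3 + 1 = 4/3. Share = (4/3)/4 = 1/3, that is 8 of 24 positions. For 160 women: 160 × 1/3 = 53.3. An incomplete last block in a hospital lowers this slightly.

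**Best-guess accuracy.** Always guess the arm with more places left. The chances of being right are 1/2, 2/3, 2/3 (= 1/3 × 1 + 2/3 × 1/2) and 1. Mean = (1/2 + 2/3 + 2/3 + 1)/4 = 17/24 = 70.8%, against 50% under simple randomisation.

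**Share certain at inclusion.** Inclusion precedes baseline and allocation follows it, so other women may be pending in between.

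- None pending ahead in that hospital: 1/3.
- One pending ahead: only the woman in 4th place can be certain, and only if the first two allocations match. Share = (1/3)/4 = 1/12.
- Two or more pending ahead: 0.

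**Illustration of the pending effect (assumed accrual).** Take 27 months of recruitment (October 2007 to December 2009, Setting), three equal strata and Poisson arrivals. The 27 months are about 117.4 weeks, so the rate is 160/(3 × 117.4) = 0.454 per week per hospital. With a constant gap of g weeks from inclusion to allocation and λ = 0.454g, the certain share is e^(−λ)/3 + λe^(−λ)/12.

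- g = 1: 0.635/3 + 0.288/12 = 0.236, about 38 women.
- g = 6: λ = 2.73; 0.065/3 + 0.178/12 = 0.037, about 6 women.

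The range of 1 to 6 weeks comes from a first visit at 9 to 12 weeks (Control group), a call up to two weeks later (Recruitment) and baseline at about 15 weeks (Outcome measurements): 15 − 9 = 6 and 15 − (12 + 2) = 1.

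**Effect of varying the block size.** Simulation with 54 women per hospital, 1,500 runs, and an observer who knows the set of possible sizes and every past allocation but not the size of the current block:

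| Block sizes | Certain | Best guess correct |
|---|---|---|
| 4 only | 32.2% | 70.3% |
| 4 and 6 | 5.5% | 69.0% |
| 4, 6 and 8 | 2.3% | 67.8% |

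The first row is just under the exact 33.3% and 70.8% because 54 is not a multiple of 4.

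**The case against.** **Roles.** A reader might infer that the staff who include the women know one allocation in three in advance. The article does not support that. Referring clinicians do the first screening on the coupon, the inclusion step is worded without an actor, and nothing says that the caller is the assistant who announces allocations, knows the block size or keeps a tally by hospital. A condensed article may well leave such roles to the full protocol. This stands. What also stands is that nothing in the text separates the roles.

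**The 53 is a ceiling.** It applies just before allocation. At inclusion the illustration gives roughly 6 to 38 women. To approach the ceiling, staff would have to influence attendance at, or the order of, baseline visits, which are planned for about 15 weeks. This stands too, but the lower figures are not zero.

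**Existing safeguards.** Allocation already follows baseline and the programmer holds the key, so asking for later release would add little. Baseline glucose is measured before allocation, and the Statistical analysis section provides for confounders, so imbalance in measured factors could be seen and adjusted for. Imbalance in unmeasured factors, such as motivation, could not.

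**Design choice.** Small fixed blocks keep the arms balanced in strata of about 53 women (160/3), a legitimate aim. Varying the sizes also barely changes guessing accuracy. Both are true; the gain lies in the certain allocations.

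**Conclusion.** The point holds as a risk. With one fixed block size of four and unblinded research staff, up to 33% of allocations, at most about 53 of 160, are deducible just before they are made. This assumes 1:1 blocks and an observer who knows the block size and every earlier allocation in that hospital. If one other woman is pending ahead, the share at inclusion is 1/12; with two or more it is zero.

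A reader might go further and conclude that selection bias has occurred or is likely. The documents do not support this: the figures measure predictability, not bias, and give no size for any effect on fasting glucose or birth weight. The matter is a cheap improvement to the concealment of allocation, not an error that undermines the design.

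**What to change.** For all blocks not yet started, draw the block size at random within each hospital, for example from 4 and 6, or from 4, 6 and 8. Only the programmer should know the sizes, and they should be withheld from the researcher and research assistant. Allocation after baseline is already planned and needs no change.

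The gain is a fall in certain allocations from 33% to about 5.5% (4 and 6) or 2.3% (4, 6 and 8). Best-guess accuracy falls only from 71% to about 69% or 68%, so the change should not be presented as removing predictability.

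The cost is regenerating the remaining schedule and a slightly larger possible imbalance. The maximum within a hospital is half the largest block, so it rises from 2 to 3 (4 and 6) or 4 (4, 6 and 8). Sample size, visits, intervention and analysis are unaffected.

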### Blinding

The key of coding concerning group assignment will only be known to the programmer of the database. The researcher and research assistant will not be blinded for allocation after randomisation. All outcome measures will be assessed by independent examiners, unaware of group allocation. Participants cannot be blinded for the intervention, but will be asked not to reveal information about their treatment to the examiners. Also obstetricians and midwifes cannot be blinded for the allocated treatment. Analyses will be performed blind for treatment allocation.

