**Figure 3 F3:**
[figure not shown]
**Formula**. A: lifted weight; B: percentage of intensity.

ACSM recommends to not do a maximal aerobic exercise test in nonclinical settings during pregnancy [25]. During pregnancy maximal heart rate reserve decreases and resting heart rate increases. This makes the standard training HR formulas ineffective [25]. ACOG and Canadian guidelines therefore recommend the use of ratings of perceived exertion (RPE) in addition to heart rate [23,26]. Borg's conventional 6–20-point scale is recommended, with 12 to 14 (a rating of 13 corresponds to a subjective rating of "somewhat hard") identified as the RPE range to apply in pregnancy [27,28]. The PARmed-X form pregnancy document modified the target HR zones for exercise prescription from the suggested target HR zones for nonpregnant individuals. The target HR zone suggested for women aged 20–29 yr is 135–150 bpm and for women aged 30–39 yr 130–145 bpm [29]. These target HR zones during pregnancy represent approximately 60–80% of aerobic capacity based on age [23]. A check to avoid overexertion will be the "talk test". The exercise intensity is too high if the exercising pregnant woman is not able to carry on a verbal conversation [23,29]. Aerobic training will be executed on cycle ergometers, treadmills, cross-trainers, and when still possible with the pregnant belly, on stationary rowing machines. For every aerobic exercise a baseline level of intensity will be estimated. This prediction will be done as follows: for example a woman starts cycling at a low work rate of 50 watt with a pedal rate at 50 rpm. The physiotherapist increases the work load till an intensity is reached that equals a Borg scale rating of 12. Woman than maintain cycling for 10 minutes on that intensity. Exercises in the subsequent session will start on that baseline intensity. When the RPE is rated under 12, the intensity will be increased by increasing the working load. At each training, attendance and the intensity of all strength and aerobic exercises will be registered by the physiotherapist.

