### Process evaluation

To assess factors that contribute to the success or failure of the program, a process evaluation will be performed. Trainers and a subgroup of 20 women will be interviewed about their experiences with the exercise program. Attendance to the exercise sessions will be recorded by the physiotherapists. Furthermore, 10 women who have declined to participate in the RCT will be interviewed about their reasons for declining, and their possible barriers towards participating in an exercise program.

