### Statistical analysis

Longitudinal, linear regression analyses will be performed. In these analyses, the correlation between multiple measurements within one individual is taken into account. The regression coefficient reflects the average difference in the outcome variable between conditions. Possible confounders will be entered into the regression analyses. Confounding will be defined as a change in the regression coefficient of 10% or more. Possible effect modification will be studied as well, defined as a significant (p < 0.10) interaction-term between group allocation and the variable concerned. Data will be analysed according to the intention-to-treat principle.

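### Blind analysis is claimed but not reconciled with unblinded staff and arm-revealing data, and covariates are chosen by their effect on the treatment coefficient

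*Protocol article*

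**What the plan says.** Three statements stand together in the Blinding section of the protocol article:

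- on the code: "The key of coding concerning group assignment will only be known to the programmer of the database";
- on staff: "The researcher and research assistant will not be blinded for allocation after randomisation";
- on analysis: "Analyses will be performed blind for treatment allocation".

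The Randomisation section adds: "After baseline measurements, a research assistant will inform the women about the group they will be allocated to".

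Two places describe data that can exist in one arm only. Under Intervention Group, in the text after Figure 3: "At each training, attendance and the intensity of all strength and aerobic exercises will be registered by the physiotherapist". Under Process evaluation: "Attendance to the exercise sessions will be recorded by the physiotherapists".

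The Statistical analysis section sets the covariate rule: "Confounding will be defined as a change in the regression coefficient of 10% or more". It also says what that coefficient is: "The regression coefficient reflects the average difference in the outcome variable between conditions". The Questionnaire section gives the candidate confounders only as examples, five of them (parity, age, ethnicity, working status, socio-economic status). Effect modification is judged by an interaction at p < 0.10, and the variables to be tested are not listed.

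**The concern.** There are two linked problems.

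First, the claim of blind analysis carries no qualification, but staff on the research team know the allocations and the data include fields that identify the intervention arm. With only two groups, a coded label gives little protection: one record of known allocation, or one attendance field, decodes both labels for the whole file. A reader cannot tell from the article what the blind consists of.

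Second, the analysis leaves choices to be made after the data are seen: which candidates are considered, which of them enter, and which interactions are examined. The quantity that decides entry is the treatment effect itself. Blinding limits an analyst's ability to steer such choices towards benefit, so its unclear status matters more here than it would with a fixed model. The rule also has a statistical cost that does not depend on who applies it. In a randomised trial a baseline covariate is imbalanced only by chance. A change-in-estimate rule tends to leave out prognostic covariates when they happen to be balanced, and then the standard error still carries the variance they would have explained.

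**Working it through.** **Can the Blinding statements stand together?** It depends on what the key is.

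- If the key is the knowledge of which woman is in which arm, the statement that only the programmer has it conflicts with the statement that the researcher and assistant are unblinded, and with the assistant telling women their group.
- If the key is the link between a code in the database and the arm, the statements are compatible. The staff know allocations from running the trial, and the analysis uses coded labels. The blind then holds only if the analyst is not one of those staff and the file lacks attendance, training and process data. The article states neither condition.

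**What does the covariate rule do?** The article gives no figure for this, so it was simulated. From the article: 64 per group (Sample size), the five named candidates (Questionnaire) and the 10% threshold (Statistical analysis). Assumed: independent covariates jointly explaining a share R² of outcome variance, and a single-time-point linear model in place of the longitudinal one. The rule was applied by screening each candidate singly against the unadjusted coefficient. The number of possible adjustment sets is 2^5 = 32.

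Rejection rates with no true effect, 1500 replicates per column:

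| Strategy | R² 0.1 | R² 0.3 | R² 0.5 |
|---|---|---|---|
| All five fixed in advance (nominal 0.05) | 0.050 | 0.047 | 0.040 |
| 10% rule, mechanical (nominal 0.05) | 0.051 | 0.040 | 0.026 |
| Smallest p of 32 sets (nominal 0.05) | 0.098 | 0.149 | 0.201 |
| Any of 32 sets favouring the intervention (nominal one-sided 0.025) | 0.048 | 0.072 | 0.109 |

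The Monte Carlo standard error at 0.05 is √(0.05 × 0.95 / 1500) = 0.0056. The mechanical rule at R² 0.5 is therefore (0.05 − 0.026)/0.0056 ≈ 4.3 standard errors below nominal. At R² 0.1 there is no effect. Swapping the arm labels changed the selected covariates in 0 of 4500 replicates.

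The last row is about half the row above it (0.098/2 = 0.049, 0.149/2 ≈ 0.075, 0.201/2 ≈ 0.10). The inflation comes from free choice among models, and an analyst who sees only A and B could produce it too. Knowing the arms adds the direction.

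A second simulation took R² from 0.3 to 0.5 and a true effect of about 0.46 SD. That effect is a little below the plan's own standardised differences (0.4/0.7 = 0.57 for glucose, 300/600 = 0.50 for birth weight).

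- With no effect, the mechanical rule rejected in 0.033 to 0.039, against 0.05.
- With the effect, its power was 0.80 to 0.89, against 0.85 to 0.94 for adjustment fixed in advance. The loss is 0.85 − 0.80 = 0.94 − 0.89 = 0.05.
- For comparison, unadjusted power by the normal approximation is Φ(0.46 × √(64/2) − 1.96) = Φ(0.64) ≈ 0.74. The rule keeps part of the gain from adjustment.

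**The case against.** The strongest reply is that the article contains no contradiction. Staff who run a trial may know allocations while someone else analyses a coded file. The article never says that the unblinded researcher is the analyst, and an intention-to-treat analysis does not need attendance data. Who runs the analysis and how the file is built are matters that an article commonly leaves to the full protocol or analysis plan. All of this stands. A reader might infer that the blind is bound to fail, or that the three Blinding statements cannot all be true. The documents do not support either inference, and not naming the analyst is not counted as a fault here. What remains is that an unqualified claim sits beside statements that undercut it on one natural reading.

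On the covariate rule, the reply is that it sets numerical thresholds, treats the two arms symmetrically, and did not inflate type I error when followed mechanically. That also stands. A reader might take the 32 adjustment sets as a measure of bias. They are only a count, and the article does not grant free choice among them. The inflated rates in the last two rows of the table assume deliberate selection. The reply does not meet two points: the candidate list is open, and the mechanical rule itself can cost power.

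**Conclusion.** The point holds in a limited form. The article claims blind analysis without reconciling it with unblinded staff and arm-revealing data. It does not show that the blind was or would be broken, and a stripped, coded file in the hands of a separate analyst would satisfy the claim.

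The covariate rule is a weak choice for the primary analysis. It leaves discretion over which candidates are considered. Applied mechanically, it gave type I error of 0.033 to 0.039 against 0.05 and about 5 percentage points less power than adjustment fixed in advance. Those figures rest on assumed R² of 0.3 to 0.5, five independent covariates and a single-time-point model. With R² of 0.1 the rule's type I error was nominal. The loss is in precision; the simulations give no sign of false positives from the rule as written. This is a clarification together with an inexpensive improvement to the analysis.

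**What to change.** 1. Reword the Blinding section so that its statements agree. Say what the key is, and that the analysis is done by someone other than the unblinded researcher and research assistant, on a file without attendance, training or process-evaluation data. If this will not be done, delete the claim of blind analysis.
2. In the Statistical analysis section, replace the 10% rule for the primary analysis with a closed list of baseline covariates. List the effect modifiers to be tested as well.
3. Fix and date the covariates, modifiers and model code on a file without the group variable. The programmer, who holds the key, then merges the group variable and the fixed code is run.

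This needs no extra participants or measurements, but it is more than a change of wording. The 10% rule cannot operate without the group variable, so it is dropped from the primary analysis, and results are slightly delayed. A person separate from the unblinded staff is needed only if the claim of blind analysis is kept.

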### Intervention

#### Intervention Group

Participants randomised to the intervention group will complete an exercise program on two days of the week during the remaining duration of the pregnancy. Each session will last for 60 minutes. The exercise program will consist of aerobic and strength exercises that will help to control the blood glucose level. All sessions will be completed under the guidance and supervision of a specifically trained physiotherapist. The sessions will be located at the Department Physiotherapy of the participating hospitals (VUMC, OLVG and SLAZ).

At the first session the participants will be introduced to the exercise program. They will be informed about the structure of the sessions and will receive instructions in the use of the equipment. Each exercise session will begin with a warming-up for 5–10 minutes. This is a light intensity activity, such as slow cycling at a level of intensity of 50 Watt, that prepares the muscles for exercise. After the warming-up, each participant completes an individualised program of 40 minutes, consisting of 1 or 2 aerobic exercises and 4 to 6 strength exercises. After exercising, participants cool down for 5–10 minutes by slowly reducing the activity. This allows the heart rate to return to normal levels.

At the start of the intervention exercises will be adjusted to maximal muscle strength and aerobic capacity of the women. However, during pregnancy it is not possible to determine maximal muscle strength and aerobic capacity levels with standard physical tests because of the pregnancy related physiological changes. The one Repetition Maximum (1-RM; the heaviest weight that can be lifted only once) weight lifting test to measure muscular strength cannot be used during pregnancy. Woman should avoid overly vigorous activity, because most pregnant women have a decreased tolerance for weight-bearing exercise and they should avoid the Valsalva maneuver during resistance exercise [7,23]. Therefore 1RM for each strength exercise will be predicted from the Oddvar Holten diagram [24]. In short this prediction is done as follows: the physiotherapist makes an estimation of the weight that can be lifted for 10–20 times; the number of repetitions that can be maximally performed is registered; the percentage of intensity can than be looked up in the Oddvar Holten diagram at the number of repetitions (figure 2) and 1RM can be computed by the formula (figure 3). For example, if a participant makes 16 repetitions with 24 kilos [i.e. 75% of 1 RM in the diagram] than, divide 24 by 0.75 for a 1RM of 32 kilos. To start an exercise program for example at 30% of 1RM: multiply the 1RM by 30%; in this case 32 times 0.30 equals 9.6 kilos. Consequently, participants will start exercising at a training load of 30% of 1RM with 15 repetitions, for 3 sets. Exercises will progress by first increasing the number of repetitions (from 15 to 30) and than by increasing the number of sets of repetitions (from 3 to 5). The training load will be increased (from 30 to 60% of 1RM) when the desired number of (sets of) repetitions with the current load is reached. For strength training, participants will use free weights and different machines to target major muscle groups in the upper body, thrunk and lower body.

